### Data analysis

Initial analyses will compare the frequency of baseline levels of outcome and other key variables (e.g., demographic and disease characteristics) for the two groups using a simple chi-square test (for categorical variables), t-test (for continuous variables with an approximately normal frequency distribution) and the Mann-Whitney-U test for continuous, non-normally distributed variables. Evaluation of intervention effectiveness will be by intention to treat using the above statistical tests. Evidence of clustering by clinic site and primary care provider will be examined and adjusted for analyses as needed. If significant differences in baseline characteristics are found, analyses will be repeated adjusting for these differences using ANOVA and logistic regression for multivariate analyses. Sensitivity analyses will be performed to estimate the effects of missing data using different assumptions (e.g., imputed values). Additional analyses will be conducted to look for evidence of effect modification by pre-specified subgroups: baseline HbA1c (< median, > median) and by English as primary language (Y/N).

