### Sample size calculation

Sample size and power calculations were performed for the main outcome of interest - difference in mean HbA1c levels - using effect sizes and standard deviations derived from multiple published trials of patient-education interventions. The recent meta-analysis by Deakin et al. of 11 such studies found a mean difference in HbA1c of 0.8% [14]. Analysis of Family Health Center patients with HbA1c values 8.0% or higher showed a standard deviation of 1.9. Using a conservative assumption of an effect size of 0.6 for percent HbA1c, we would need 180 subjects in each arm to achieve a power of .85 using the standard threshold for a significant difference of .05 (2-sided). To account for a 10% loss to follow-up, we will enroll 200 subjects in each arm.

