### Outcome measures

Outcomes variables are measured at baseline and at 6 months. Peer coaches are assessed at 12 months. The primary outcome is change in HbA1c. Secondary outcomes include change in: systolic blood pressure, BMI, LDL, diabetes self-care activities, medication adherence, diabetes-related quality of life, diabetes self-efficacy, and depression.

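### The primary test for HbA1c change is left to a distribution-dependent rule, and one branch of that rule (Mann-Whitney U) does not test the mean difference the trial was sized for

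*Protocol article*

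**What the plan says.** All references are to the protocol article.

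- **Outcome measures:** "The primary outcome is change in HbA1c", with outcomes measured at baseline and 6 months.
- **Sample size calculation:** "Sample size and power calculations were performed for the main outcome of interest - difference in mean HbA1c levels". The inputs are a target difference of 0.6 HbA1c percentage points, an SD of 1.9 and a two-sided 5% level. The result is "we would need 180 subjects in each arm to achieve a power of .85", raised to 200 per arm for 10% loss to follow-up.
- **Data analysis:** the section opens with tests for comparing the arms at baseline: chi-square for categorical variables, a t-test for continuous variables that are close to normal, and "the Mann-Whitney-U test for continuous, non-normally distributed variables". The efficacy comparison then takes over the same list: "Evaluation of intervention effectiveness will be by intention to treat using the above statistical tests".

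No test is assigned to HbA1c. There is no criterion for approximate normality, and no statement of whether it is judged on baseline, 6-month or change values. The other between-arm models named are ANOVA and logistic regression, for repeat analyses if baseline differences turn out significant. They do not settle the primary test.

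**The concern.** The sizing and the analysis rule do not fully fit each other. The sizing fixes the quantity of interest as a difference in mean HbA1c. The analysis rule allows a test of a different hypothesis. Mann-Whitney U asks whether values in one arm tend to exceed those in the other; it neither tests nor estimates a difference in means unless the two distributions have the same shape.

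Two things are at stake. First, the report could carry a primary p-value from ranks beside a mean difference and confidence interval from another method, and the two need not agree. Second, the primary test is not fixed in advance, which leaves some discretion to the analyst. This goes beyond detail an article may leave to an analysis plan, because the article states a rule and that rule sits awkwardly with its own sample size section.

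**Working it through.** **1. Reproduce the stated sample size.** Inputs from Sample size calculation: difference 0.6, SD 1.9, two-sided alpha 0.05, power 0.85.

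n per arm = 2 × (z₀.₉₇₅ + z₀.₈₅)² × (SD/difference)² = 2 × (1.960 + 1.036)² × (1.9/0.6)² = 2 × 8.978 × 10.028 ≈ 180.07, which rounds up to 181. The plan says 180.

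Power at 180: standard error = 1.9 × √(2/180) = 0.2003; 0.6/0.2003 = 2.996; 2.996 − 1.960 = 1.036; power 0.850. Enrolment: 180/0.90 = 200. The plan's figures are those of a two-sample comparison of means.

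**2. Do the two branches test the same thing?** Simulation, 180 per arm, SD 1.9, 5000 runs; the shapes are assumptions. Equal means, different shapes, rejection at 5%:

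| Shapes in the two arms | t-test | Mann-Whitney |
|---|---|---|
| normal vs gamma (shape 2) | 0.050 | 0.170 |
| normal vs gamma (shape 4) | 0.049 | 0.116 |
| gamma 4 vs gamma 2 | 0.056 | 0.058 |

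With no difference in means, Mann-Whitney can reject well above 5%, because it addresses another hypothesis.

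**3. Does choosing by distribution inflate type I error?** Same simulation, no effect, same shape in both arms, with the test chosen by Shapiro-Wilk on residuals (an assumed criterion; the plan gives none). Over normal, t with 5 df, gamma 4 and gamma 2 shapes, the t-test rejects in 0.047 to 0.052, Mann-Whitney in 0.045 to 0.051 and the chosen test in 0.045 to 0.052 of trials. There is no material inflation.

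**4. Does Mann-Whitney lose power?** Mean benefit of 0.6, same simulation:

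| Shape | Uniform shift: t / MW | Benefit in 25% of patients: t / MW |
|---|---|---|
| normal | 0.850 / 0.833 | 0.806 / 0.743 |
| t, 5 df | 0.843 / 0.908 | 0.791 / 0.789 |
| gamma 4 | 0.851 / 0.899 | 0.791 / 0.771 |
| gamma 2 | 0.837 / 0.946 | 0.804 / 0.809 |

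Neither test is better throughout.

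**5. What does a fixed, baseline-adjusted mean comparison give?** Assumed model: baseline = 8 + gamma (shape 1.2, SD 1.9); 6-month value = 9 + 0.5 × (baseline − 9) + normal error with SD 1.6.

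- Variance of change = 0.25 × 3.61 + 2.56 = 3.4625 (SD 1.861). Variance after baseline adjustment = 2.56 (SD 1.6).
- Uniform 0.6 benefit. t-test on change: SE = 1.861 × √(2/180) = 0.196, ratio 3.059, power 0.864. ANCOVA: SE = 1.6 × √(2/180) = 0.169, ratio 3.558, power 0.945. Simulation (2000 runs): 0.87 and 0.94, with Mann-Whitney on change at 0.86.
- Benefit of 2.4 in 25% of coached patients (mean 0.6), which adds 2.4² × 0.25 × 0.75 = 1.08 to the coached arm's variance. t-test: SE = √((3.4625 + 4.5425)/180) = 0.211, power 0.812. ANCOVA: SE = √((2.56 + 3.64)/180) = 0.186, power 0.898. Simulation (2000 runs): 0.80 and 0.89, with Mann-Whitney at 0.75.
- No effect: the t-test alone and the normality rule both reject in 0.058 of the 2000 runs (Monte Carlo standard error √(0.05 × 0.95/2000) ≈ 0.005).

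Under the uniform shift, moving from Mann-Whitney to the t-test gains 0.01, while moving from the t-test to ANCOVA gains 0.07. That gain is due to the baseline adjustment.

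**The case against.** The strongest defence is that the test list is generic wording covering nine change outcomes, several of them questionnaire scales, and that a fuller document could assign the t-test to HbA1c. That branch is consistent with the sizing, where the target is "the main outcome of interest - difference in mean HbA1c levels". This stands in part: the conflict arises only if the Mann-Whitney branch is used. But nothing in the article rules that branch out for the primary outcome.

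A reader might infer several stronger charges that the article does not support:

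- **The test is chosen on unblinded outcome data.** The trial is described as unblinded, but nothing says who judges the distribution, when, or on which data.
- **The 8% eligibility floor makes a switch likely.** The floor applies to a value from the 6 months before enrolment, not to change. In the assumed model of step 5, baseline has skewness 2/√1.2 = 1.83, but change has only −(0.95³ × 1.83)/1.861³ ≈ −0.24. Shapiro-Wilk then rejects normality in roughly 37% to 46% of trials, so a switch is possible but far from certain. The 90% to 100% rejection rates in the simulation of steps 2 to 4 belong to heavy-tailed or skewed shapes assumed directly.
- **The choice materially inflates false positives.** An honest rule does not. Even always reporting the smaller of the two p-values gave only 0.060 to 0.063 under no effect in the step 5 model.
- **Mann-Whitney wastes power.** It does so in some concentrated-benefit scenarios, which the article does not posit, and gains power under a uniform shift with skewed or heavy-tailed data.
- **Mann-Whitney cannot adjust for baseline, clinic or coach.** Nor can the plain t-test, so this does not separate the two. The Data analysis section provides separately for clustering by clinic and provider; clustering by coach is a different matter.

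**Conclusion.** The point holds in a limited form. The article sizes the trial on a mean difference but carries into the primary comparison a rule with one branch that does not test it, and does not say which branch applies to change in HbA1c. The consequence is an unfixed primary test and a possible mismatch between p-value and reported effect. It is not a demonstrated error-rate problem or a general loss of power.

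The sizing check uses only the plan's figures. Every error-rate and power figure beyond it rests on assumed distribution shapes, an assumed normality criterion and, for the ANCOVA figures, an assumed slope of 0.5 on baseline and residual SD of 1.6. A weaker baseline to follow-up relation, with a larger residual SD, would change the ANCOVA figures. At 180 per arm the t-test stayed close to its nominal level in the shapes tried, so normality need not drive the choice. Severity is minor to moderate, and the improvement is essentially free.

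**What to change.** In Data analysis, name one primary analysis for HbA1c that applies whatever the distribution: the between-arm mean difference in 6-month HbA1c, adjusted for baseline HbA1c by ANCOVA, with robust standard errors if wanted. With baseline in the model, the arm effect is the same whether the dependent variable is the 6-month value or the change, so the stated primary outcome is respected. Keep Mann-Whitney U on change as a labelled sensitivity analysis.

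The cost is a sentence or two of wording. Baseline HbA1c is already collected, and the sample size stays at 180 analysed and 200 enrolled per arm. Clustering by coach should be dealt with separately and is not needed for this change.

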### Intervention

Patients in the active arm are paired with a peer coach for six months, receive phone calls from coaches at least twice a month, meet face to face at least twice, and if possible, are accompanied to at least one clinic visit. Additional calls and meetings are at the discretion of client and coach. Coaches document each encounter attempt and record: date, the nature of encounter (phone or in person), approximate duration of contact, and topics discussed.

The first encounter is a phone call during which coaches introduce themselves and begin to establish a relationship with the client before discussing diabetes. In subsequent interactions the coach and client discuss: current and target clinical values for HbA1c, LDL cholesterol and blood pressure; self management skills such as using a glucometer and appropriate strategies for hypoglycemia; taking medications as prescribed; and lifestyle changes around healthy eating, physical activity, and stress. Coaches and clients may also share stories about family, careers, and hobbies.

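### The stated primary test on change in HbA1c does not condition on baseline HbA1c, which leaves it open to bias from baseline-related dropout and costs precision

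*Protocol article*

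**What the plan says.** All references are to the protocol article.

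- **Outcome measures:** "The primary outcome is change in HbA1c", and "Outcomes variables are measured at baseline and at 6 months". No intermediate HbA1c is described for patients.
- **Data analysis:** "Evaluation of intervention effectiveness will be by intention to treat using the above statistical tests". The tests just named are chi-square, the t-test and Mann-Whitney U. Analyses are repeated with adjustment only where baseline characteristics differ significantly between the arms.
- **Data analysis, on missing values:** "Sensitivity analyses will be performed to estimate the effects of missing data using different assumptions (e.g., imputed values"). No rule is given for how a patient without a 6-month HbA1c enters the main comparison.
- **Sample size calculation:** 180 per arm are needed. "To account for a 10% loss to follow-up, we will enroll 200 subjects in each arm". Loss is not split by arm.
- **Intervention:** coached patients "receive phone calls from coaches at least twice a month, meet face to face at least twice". The usual-care arm has no matching contact, and the trial is unblinded.

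**The concern.** A two-sample test on change needs both HbA1c values. Unless a value is imputed, a patient without the 6-month measurement drops out of the comparison. Imputation is named only for sensitivity analyses, and the sample size counts 180 of 200 per arm after loss, so the main test most naturally uses observed cases.

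Patients are selected for a high HbA1c, so change is related to baseline: those who start higher tend to fall further. If dropout removes high-baseline patients from one arm more than from the other, the mean change in the two arms shifts unequally even when coaching does nothing. The much greater contact in the coached arm makes unequal retention plausible.

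The planned baseline check is not built to catch this. Read naturally, it compares the arms as enrolled, where randomisation makes a significant difference unlikely. It need not see an imbalance that arises later through loss. So the adjustment that would remove this bias hangs on a trigger that may never fire. That trigger also forgoes precision available from a baseline value the trial already collects.

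**Working it through.** **1. The plan's own figure.** Inputs are the plan's effect ("Using a conservative assumption of an effect size of 0.6 for percent HbA1c"), its SD ("Analysis of Family Health Center patients with HbA1c values 8.0% or higher showed a standard deviation of 1.9"), two-sided alpha 0.05 and power 0.85.

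n per arm = 2 × 1.9² × (1.960 + 1.036)² / 0.6² = 180.07, which rounds up to 181. The exact t-test gives 181.03, and power at 180 is 0.850 (normal) or 0.848 (t). Inflation: 180 / (1 − 0.10) = 200. The stated 180 and 200 reproduce. About 20 per arm, or 40 of 400, are expected to lack the outcome.

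**2. Bias when loss depends on baseline.** None of these inputs is in the article; all are assumed:
- loss of 15% in controls and 5% in coached patients (10% overall, as planned)
- control dropout odds multiplied by 1.5 or 2 per SD of baseline HbA1c; coached dropout unrelated to baseline
- SD 1.9 at both times, linear relation, correlation r of 0.3, 0.5 or 0.7.

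With logistic dropout p(z) averaging 15%, the mean standardised baseline among control completers is E[z(1 − p(z))] / 0.85. This is −0.0596 for an odds ratio of 1.5 and −0.0978 for 2. Times 1.9, that is −0.113 and −0.186 HbA1c points.

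Shift in mean control change = −(1 − r) × shift in mean baseline:

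| r | Odds ratio 1.5 | Odds ratio 2 |
|---|---|---|
| 0.3 | 0.7 × 0.113 = +0.079 | 0.7 × 0.186 = +0.130 |
| 0.5 | 0.5 × 0.113 = +0.057 | 0.5 × 0.186 = +0.093 |
| 0.7 | 0.3 × 0.113 = +0.034 | 0.3 × 0.186 = +0.056 |

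Controls appear to fall less than they did, so the bias favours coaching by 0.03 to 0.13 points, or 6% to 22% of 0.6. Simulating 2,000,000 control patients gave the same values to within about 0.002. Regressing 6-month HbA1c on baseline in the *same completers* cut the shift to 0.002 or less in every case.

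Effect on type I error at r = 0.5, where the SD of change is 1.9: with 170 and 190 completers, SE = 1.9 × √(1/170 + 1/190) = 0.201. A bias of 0.09 raises the two-sided error from 0.05 to about 0.07.

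**3. Other assumptions, other signs.**
- Equal loss and equal dropout outcomes in both arms: bias 0.
- Same 15%/5% loss, but dropouts in both arms do 1.0 point worse than completers for unobserved reasons. Completers flatter controls by 0.15 × 1.0 = 0.15 and coached patients by 0.05 × 1.0 = 0.05. Net: 0.10 *against* coaching.
- Loss reversed (15% coached, 5% control), same 1.0 point: 0.10 in favour of coaching.
- Scenario of step 2, but comparing 6-month levels: the control mean shifts by r × (−0.113 or −0.186), or −0.03 to −0.13, the opposite sign to change.

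**4. Precision.** SD of change = 1.9 × √(2(1 − r)). Residual SD after conditioning on baseline = 1.9 × √(1 − r²). Power for 0.6 at 180 per arm, two-sided 0.05, t distribution:

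| r | SD of change | Power, change | Residual SD | Power, ANCOVA |
|---|---|---|---|---|
| 0.3 | 2.25 | 0.71 | 1.81 | 0.88 |
| 0.5 | 1.90 | 0.85 | 1.65 | 0.93 |
| 0.7 | 1.47 | 0.97 | 1.36 | 0.99 |

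The article gives no correlation. Using the single-time SD of 1.9 for change amounts to assuming r = 0.5; below that, the planned 0.85 is not reached with change scores.

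**The case against.** A reader might infer that the headline result is a completer analysis mislabelled as intention to treat. The article does not support that. It names an analysis principle and tests, not the data set they run on. A t-test can be applied to imputed data, and inflating 180 to 200 for loss is routine under any missing-data method. Observed-case analysis is the natural reading, not a stated rule. The missing-data rule may also sit in a full protocol or analysis plan that is not shown, so its absence here is no fault.

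Nor do the numbers support that label as the diagnosis. Conditioning on baseline removes the bias in step 2 while leaving out exactly the same patients. The weakness is the lack of conditioning.

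A reader might also infer that the result will favour coaching. The 15%/5% split and the odds ratios are assumptions, and step 3 shows zero and opposite signs under others equally open. Even the largest figure in step 2 is below one standard error of the difference (about 0.16 to 0.24 across these correlations).

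Finally, the plan already commits to sensitivity analyses under several missing-data assumptions. That is a real safeguard, but a sensitivity result that disagrees does not change the declared primary one.

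What survives is a stated choice rather than a silence: unadjusted tests, with baseline adjustment made conditional on significance.

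**Conclusion.** The point holds in a limited form. The primary comparison, as stated, does not condition on baseline HbA1c unless a significance test triggers it. If it uses observed cases, it is exposed to a bias of about 0.03 to 0.13 points under the assumed baseline-related loss. The bias is zero if loss and dropout outcomes match across arms, and about 0.10 against coaching in the not-at-random case. The direction is undetermined and the size modest against 0.6.

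The loss of precision needs no assumption about dropout, only about the correlation: power of about 0.71 to 0.97 for change against 0.88 to 0.99 with adjustment. These figures assume SD 1.9 at both times and a linear relation. Conditioning on baseline does not cure loss for unobserved reasons; only the sensitivity analyses address that.

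**What to change.** - Make the primary analysis a comparison by assigned arm of 6-month HbA1c conditioned on baseline HbA1c, regardless of baseline significance tests. Use ANCOVA, or an equivalent likelihood-based model with a common baseline mean. In ANCOVA the treatment estimate is the same whether the outcome is entered as change or as the 6-month level.
- State which patients enter it and how those without a 6-month HbA1c are handled, unless another document already does so.
- Keep the unadjusted test as a supportive analysis.
- In the sensitivity analyses already planned, vary the assumption about missing 6-month values separately by arm, and report loss by arm.

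The cost is wording and a little more analysis work. No new patients, visits or measurements are needed. The downside is reliance on values being missing at random given baseline; the by-arm sensitivity analyses test how far the conclusion depends on it.

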#### Patients

Prior to patient enrollment, the study team creates a randomization system to ensure unbiased sorting of patients to each study arm: to receive peer coaching vs. to receive usual care.

A language-concordant study team member contacts eligible patients by phone one week proceeding mailings. Patients who do not respond to letters or phone calls are approached at their next scheduled clinical appointment. Eligible patients who opt to participate are screened to ensure that he/she: (1) is willing to work with a peer coach if randomized to the coaching arm, (2) plans to reside in San Francisco for the next 6 months, (3) plans to continue receiving care at his/her assigned clinic for 6 months, (4) has a telephone, and (5) is not currently enrolled in a diabetes management program or study. Patients who answer yes to all of the above are given IRB-approved informed consent for enrollment into the study.

All participants complete a baseline survey, available on request from the authors. The study team then measures the blood pressure, weight, and height for each participant. Blood pressures are measured in the left arm after sitting for at least five minutes. The study team member obtains two blood pressure readings (with an Omron Home Blood Pressure Monitor Model 711-AC) two minutes apart, then averages the two for a final measurement. If the two systolic readings differ more than 5 points, a third blood pressure reading is measured and averaged with the two previous readings. Weight is obtained with a calibrated, portable, digital scale (HealthOmeter). Height is obtained using a tape measure and architect's right angle triangle. Participants with missing HbA1C or LDL cholesterol values in the past 6 months receive a lab requisition form to perform laboratory testing for these values.

At the completion of the consent process, patients learn the randomly generated enrollment assignment to either the active or control group. Patients in the active group select a peer coach from a coach profile. Each enrolled patient is compensated $10.

The study team notifies the peer coach by phone and provides the coach with the patient's name and contact information.

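### Peer coach is missing from the clustering levels named in the analysis and from the sample size, so the standard error and the 0.85 power hold only if coach effects are negligible or coaches see about one patient each

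*Protocol article*

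**What the plan says.** All places are in the protocol article.

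- **Data analysis.** Effectiveness is tested by intention to treat with the same simple tests used at baseline (chi-square, t-test, Mann-Whitney), all of which assume independent patients. On clustering: "Evidence of clustering by clinic site and primary care provider will be examined and adjusted for analyses as needed". No other level is named.
- **Intervention.** "Patients in the active arm are paired with a peer coach for six months". Contact beyond the minimum is left to coach and client, so the amount of coaching can differ between coaches.
- **Enrollment and randomization, Patients.** Patients learn their arm, and then: "Patients in the active group select a peer coach from a coach profile". Randomization is described for individual patients.
- **Eligibility criteria and Enrollment and randomization, Peer coaches.** Coaches are expected to work with patients, in the plural, for at least six months. No caseload or number of coaches is given.
- **Sample size calculation.** "we would need 180 subjects in each arm to achieve a power of .85", at two-sided 0.05, with a difference of 0.6 and an SD of 1.9. "To account for a 10% loss to follow-up, we will enroll 200 subjects in each arm". No ICC or design effect appears.

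**The concern.** Each active-arm patient has one coach, a coach is expected to have several patients, and control patients have none. This is a partially nested design. If some coaches are more effective than others, patients of the same coach share part of their outcome, and the active-arm mean varies more than an independence formula allows.

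The plan does address clustering, but the levels it names are ones that individual randomization leaves largely crossed with arm: clinics and providers should have patients in both groups, so ignoring them does little harm to the error rate. The coach sits in one arm only and delivers the whole intervention. Adjustment even for the named levels is made only if the data show evidence of clustering, and such a check has little power with few clusters.

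At stake are a confidence interval for the HbA1c difference that is too narrow, a test that rejects too often in favour of coaching, and a power statement that is too favourable.

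**Working it through.** **Inputs from the Sample size calculation:** difference d = 0.6, SD s = 1.9, two-sided alpha 0.05, power 0.85, n = 180 analysed per arm.

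**Step 1: reproduce the plan's figure under independence.**

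n = 2(1.960 + 1.036)² × 1.9² / 0.6² ≈ 180.1, which rounds up to 181 against the stated 180.

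SE = 1.9 × √(2/180) = 0.2003. Power = Φ(0.6/0.2003 − 1.96) = 0.850 (0.848 with the noncentral t).

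180/(1 − 0.10) = 200. The stated figures therefore reproduce, with a design effect of 1.

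**Step 2: add coach clustering in the active arm only.**

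Assumptions, because the article gives no values: 20, 30 or 60 coaches, equal caseloads m = 180/coaches, coach ICC 0 to 0.10, total SD held at 1.9, normal approximation.

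- DE = 1 + (m − 1) × ICC
- SE = 1.9 × √(DE/180 + 1/180)
- r = SE / 0.2003
- Type I error of the unadjusted test = 2[1 − Φ(1.96/r)]
- Power of a test that uses the correct SE = Φ(0.6/SE − 1.96)

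Worked case, 20 coaches and ICC 0.05: m = 9; DE = 1 + 8 × 0.05 = 1.40; SE = 1.9 × √(2.40/180) = 0.2194; r = 1.095. Type I error = 2[1 − Φ(1.789)] = 7.4%. Power = Φ(2.735 − 1.960) = 0.781.

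| Coaches (m) | ICC | DE | r | Type I error, unadjusted | Power, correct SE |
|---|---|---|---|---|---|
| any | 0 | 1.00 | 1.000 | 5.0% | 0.850 |
| 20 (9) | 0.01 | 1.08 | 1.020 | 5.5% | 0.836 |
| 30 (6) | 0.01 | 1.05 | 1.012 | 5.3% | 0.841 |
| 60 (3) | 0.01 | 1.02 | 1.005 | 5.1% | 0.846 |
| 20 (9) | 0.05 | 1.40 | 1.095 | 7.4% | 0.781 |
| 30 (6) | 0.05 | 1.25 | 1.061 | 6.5% | 0.806 |
| 60 (3) | 0.05 | 1.10 | 1.025 | 5.6% | 0.832 |
| 20 (9) | 0.10 | 1.80 | 1.183 | 9.8% | 0.716 |
| 30 (6) | 0.10 | 1.50 | 1.118 | 8.0% | 0.764 |
| 60 (3) | 0.10 | 1.20 | 1.049 | 6.2% | 0.815 |

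Unequal caseloads, which are possible when patients choose, would make these figures somewhat worse. Small-sample degrees of freedom would also lower power a little, since the table uses 1.96.

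**Step 3: which ICC counts.** The ICC in these formulas is the part caused by coaches. Patients select a coach after allocation. Regrouping an arm that has already been randomized makes members of a group look alike, but it leaves the arm mean and its variance unchanged. A simulation with 180 per arm, no treatment effect and the active arm sorted into 20 groups of 9 gave an apparent ICC of about 0.12 and a t-test type I error of 4.9% over 20,000 runs.

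**The case against.** The strongest case against has five parts.

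1. **The consequences are conditional.** A reader might infer that the standard errors are too small and that 0.85 power will not be reached. The article does not support either as fact. At ICC 0, or with one patient per coach, nothing changes; at ICC 0.01 power is still about 0.84. This stands.
2. **Type I error.** If coaching changes no patient's HbA1c, coaches induce no correlation and the unadjusted test keeps its 5% level. Inflation needs coaches who differ, an average effect of zero, and coaches regarded as a sample from a wider pool. This also stands. However, the Background states the aim as showing that peer coaching in primary care improves outcomes, which is a claim about more than the coaches who happened to be trained.
3. **Delivered power depends on more than clustering.** The 1.9 is a spread of HbA1c values in one clinic's patients, while the outcome is change in HbA1c, whose SD is not given and could move power either way. The article calls 0.6 conservative beside a published mean difference of 0.8. At 0.8, even 15 coaches with ICC 0.10 (DE = 2.1, SE = 0.249) would give power of 0.89. So a shortfall cannot be asserted outright.
4. **Other levels may absorb some of it.** If coaches map onto clinics, clinic adjustment could take up part of the coach effect. The article does not say that they do, and that adjustment is itself only as needed.
5. **A condensed article may leave model details to an analysis plan.** This would answer silence on clustering. It answers less well a sentence that lists the levels to be examined and leaves out the one tied to delivery of the intervention.

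**Conclusion.** The point holds in conditional form. The analysis names clinic and provider, to be adjusted for only as needed, and omits the coach; the sample size assumes full independence. If coaches differ in effectiveness and each has more than one patient, the planned tests understate the standard error for inference beyond these coaches, and power computed with the correct standard error is below 0.85.

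Under the assumed 20 to 60 coaches, equal caseloads and SD 1.9, the effect is trivial at ICC 0.01, modest at ICC 0.05 (a standard error 2.5 to 9.5% larger, power lower by 1.7 to 6.9 points) and material at ICC 0.10 (type I error 6.2 to 9.8%, power 0.716 to 0.815). The documents do not show where in this range the trial lies.

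Two stronger readings are not supported: that the stated power is certainly missed, and that patients' choice of coach inflates the error. Severity is moderate: a cheap correction to a prespecified rule, not a flaw that invalidates the design.

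**What to change.** **Data analysis.** Name peer coach as a level, and state that the HbA1c comparison accounts for it whatever a test for clustering shows. Suitable wording: 'The primary HbA1c comparison will use a partially nested linear mixed model with a random coach effect in the active arm only, each control patient treated as a singleton, and small-sample degrees of freedom.' Coach-robust standard errors, with each control patient as a cluster of one, are an acceptable alternative.

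**Sample size calculation.** State that 0.85 assumes no coach clustering, give the expected number of coaches and caseload, and report power over a range of coach ICC, as in the table above.

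**Cost.** No extra patients. Coach identity should already be available from the pairing and the encounter records. The confidence interval becomes slightly wider, and may be somewhat conservative, because a random coach effect cannot separate coach-caused variation from patients sorting themselves to coaches. The stated power becomes less favourable. If the coach ICC proves close to zero, little is lost.
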